#### 2.7.4 Divided attention task

During this task, participants drive for approximately 3 miles on a two-lane road with no other cars present. The posted speed limit is 55 mph (88 km/h). Periodically, symbols appear in one of four designated quadrants on the left or right monitor. Participants are instructed to respond when they see these symbols by pressing buttons located adjacent to the steering wheel (see Figure 4); a symbol appearing on the left monitor would prompt a left button response and a symbol appearing on the right monitor would prompt a right button response. A total of 20 trials will be presented to the participant, with each symbol appearing for a maximum of 5 s and disappearing once a correct or incorrect response is recorded. Participants are also instructed to try to maintain a constant lane position throughout the task. Primary outcome measures include correct responses to the presented symbols (out of 20), mean reaction time to respond to the symbols, SDLP, and SDSP (a measure of speed variability).

**FIGURE 4 F4:**
[figure not shown]
The divided attention task with arrows (red circle) that appear on the left and right monitor displays. Participants must press the corresponding buttons (see Figure 2) within a 5-s timeframe to receive a “correct” response. The primary outcomes for this scenario are SDLP, standard deviation of speed (SDSP), the percentage of correct responses, and the average reaction time to the 20 trials.

#### 2.7.5 Control straightaway segment

Following completion of the car-following task, participants continue driving on the same straight roadway for another 2 miles. The posted speed limit is 70 mph (110 km/h). This stretch of roadway is identical to the roadway used for the car-following task. The purpose of the stretch is to assess driving performance in the absence of any additional cognitive demands, thus serving as an important comparator to performance data collected under increased cognitive load (i.e., during the car following and divided attention tasks). Primary outcome measures during this segment are SDLP and SDSP.

#### 2.7.6 Crash avoidance events

As mentioned above, participants encounter a variety of environments throughout the 25-min drive such as residential neighborhoods, urban and metropolitan areas, rural areas, and construction zones. Each of the 10 drives contain three unique pre-determined crash avoidance scenarios interspersed throughout these areas. Each crash avoidance occurs in a roadway segment with a posted speed limit of 35 mph (55 km/h) and is designed to be unexpected (e.g., pedestrian or deer suddenly walking into the road, vehicle backing out into the road). The three unique avoidances in each drive are set to a different difficulty level (i.e., “easy”, “medium”, and “hard”). This allows for crash risk from using alcohol, cannabis, and alcohol and cannabis in combination to be assessed for avoidance scenarios of a range of difficulties (Figure 5).

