## 2 Methods

### 2.1 Study design overview

The study is a two-part, randomized, double-blind, placebo-controlled, crossover study examining the acute effects of oral high Δ9-THC cannabis (Part 1) or vaporized high Δ9-THC cannabis (Part 2) and alcohol, alone and in combination, on various pharmacodynamic (e.g., cognitive/psychomotor/driving performance, subjective drug effects) and pharmacokinetic outcomes. All study participants will complete seven separate outpatient sessions where they will consume a cannabis-infused brownie (containing 0, 10, or 25 mg Δ9-THC) or inhale vaporized cannabis (containing 0, 10, or 25 mg Δ9-THC) and a drink that contains placebo or alcohol (alcohol-containing drinks will be calculated to produce a BAC of 0.05%). Placebo drinks contain 1 ml of alcohol, which is placed on top of the beverage immediately prior to dosing and contain an alcohol-soaked hair tie as part of blinding procedures (to mask smell and taste sensory cues). There will also be a positive control session where participants will administer placebo cannabis with an alcohol drink calculated to produce a BAC of 0.08% (selected due to its common use as a *per se* threshold for law enforcement to enforce driving under the influence (DUI) laws). Each session will be conducted at the Johns Hopkins Behavioral Pharmacology Research Unit (BPRU), will last approximately 10 h, and will be separated by at least 1 week to allow for sufficient drug washout. Experimental procedures are approved by the Institutional Review Board of Johns Hopkins University School of Medicine (IRB00290015) and will be conducted in accordance with the Declaration of Helsinki. Part 1 is registered with ClinicalTrials.gov (NCT04931095) and the project was funded by the National Institute on Drug Abuse (R01-DA052295 to [name]).

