A total of ten unique drives were created for this project to avoid potential practice/learning effects (e.g., memorizing avoidance scenarios). Drives differ by the order with which events and scenarios are presented and by the type of accident avoidances that occur, but the drives are otherwise identical so that each version will produce comparable results. For example, the length of each drive, the environments encountered, and key drive features are the same for each simulation. Other vehicles in the simulations are randomly generated, which further increases the novelty of each drive. Beyond mitigating practice/learning effects, the different drive iterations also ensures that each drive is novel to the participant on a given session day; at each driving timepoint, participants are randomized to receive any of these 10 drives, but the same drive will not occur twice in a given session. Each drive is approximately 18 miles long and takes about 25 min to complete. All 10 versions of the driving simulation (as well as an R script to extract and organize the data) are available to download at: https://github.com/[name]/STISIM_impaired_driving. Drives will be performed at baseline and again 1.5, 3.5, 5.5, and 7.5 h after Time 0 (see Figure 1).

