**FIGURE 5 F5:**
[figure not shown]
Crash avoidance events that occur throughout the drive for **(A,B)** human avoidance scenarios, and **(C,D)** vehicle avoidance scenarios. The primary outcomes for these events are collisions, reaction time to the event, and time-to-collision with the event.

Avoidance events are programmed to trigger based on the driver’s headway time from the object (e.g., pedestrian); easy, medium, and hard avoidances are set to headway times of 3.0, 2.5, and 2.0 s, respectively. Setting all avoidances based on headway time ensures a standard duration to react to a given avoidance (regardless of their approaching speed) and allows for direct comparisons across different types of avoidances. All avoidances were designed in ways that force participants to make a response and reduce the likelihood that they can ignore the avoidance. For example, for several avoidances, participants are constrained to a single lane at the time of appearance. The primary outcome measures for the crash avoidances are reaction time and time-to-collision (TTC) with the object. Reaction time to each avoidance is based on the participant’s initial response to the object after it appears, which could be a braking or steering response. TTC is calculated based on the participant’s distance from the object at the time of their initial response and their current speed at the time of their response (i.e., distance/speed = TTC).

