### 2.14 Data presentation and statistical analysis plan

Power analyses for each primary outcome were conducted in R, using the SIMR package (Green and Macleod, 2016), which estimates power for linear mixed models by fitting a regression model multiple times under different scenarios, or simulations (100 simulations were performed for each power calculation). Effect sizes (Cohen’s d) and data (means and SDs) were obtained from prior alcohol/cannabis co-use studies (Hartman et al., 2016a) and/or prior studies conducted in our laboratory (Spindle et al., 2018; Spindle et al., 2021) that administered the proposed doses of oral/vaporized cannabis or alcohol alone. Overall, all power analyses revealed that 32 participants (16 men/16 women) in Part 1 and Part 2 would provide sufficient power (≥ 0.80 power for all 100 simulations) to test the study hypotheses stated.

For each outcome, descriptive statistics (means and standard deviations) will be generated. Linear mixed models will be used to test for differences across experimental conditions. Hypothesis tests will be two-sided, and significance will be set at *p* < 0.05. Factors entered into these models will include: Time (number of levels will differ depending on outcome variable), Alcohol Dose (0%, 0.05%, and 0.08%), Cannabis Dose (0, 10, and 25 mg Δ9-THC), and Sex (male or female). Time, alcohol dose, and cannabis dose will be within-subject factors (i.e., repeated measures); sex will be a between-subject factor. Maximum concentration (C_max_) and area under the curve (AUC) for Δ9-THC and Δ9-THC metabolites (11-OH-Δ9-THC; Δ9-THC-COOH) will be entered as covariates. Holm-Bonferroni corrections will be used to control for multiple comparisons. Data will be inspected for normality (skewness, kurtosis, outliers) and, where necessary, data transformations will be applied. Missing data is expected to be rare, as tasks and instruments are computerized, and field sobriety tasks will be video recorded. Additionally, if a participant presents elevated concentrations of Δ9-THC or Δ9-THC metabolites at baseline, and these values do not increase following active drug administration, this participant will be excluded from analysis.

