For Part 1 and Part 2, a priori planned comparisons will be conducted to compare mean peak change-from-baseline scores for each outcome for: (1) alcohol alone (BAC 0.05%) to alcohol with cannabis (BAC 0.05% + 10 mg Δ9-THC and 25 mg Δ9-THC); and 2) cannabis alone (10 mg Δ9-THC and 25 mg Δ9-THC) to cannabis with alcohol (BAC 0.05% + 10 mg Δ9-THC and 25 mg Δ9-THC). Additionally, planned comparisons will compare impairment (e.g., DRUID scores, composite drive scores) between cannabis with alcohol (BAC 0.05% + 10 m g Δ9-THC and 25 mg Δ9-THC) to the positive control condition (alcohol alone: BAC 0.08%). Correlations will be conducted to assess the relations between DRUID and driving performance. Sensitivity and specificity analyses will be conducted to characterize the effectiveness of the DRUID for determining driving impairment. Specifically, we will plot the sensitivity (true positive rate) and specificity (true negative rate) of the DRUID at identifying impaired driving by comparing various DRUID cutoffs to established cutoffs for driving simulator data that are indicative of clinically meaningful impaired driving in real-world settings (e.g., SDLP change-from-placebo ≥ 2.4 cm; Jongen et al., 2016). Sensitivity and specificity will be calculated as follows: sensitivity (100 × [TP/(TP + FN)]) and specificity (100 × [TN/(TN + FP)]).

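### Section 2.7.6 is inconsistent on whether collisions are a primary outcome; if they are, a sparse yes/no event goes into linear models and a peak score under an uncheckable 0.80 power claim

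*Protocol article*

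**What the plan says.** All of this is in the protocol article.

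- **Section 2.7.6, body text.** Each drive has three crash-avoidance events, and "The three unique avoidances in each drive are set to a different difficulty level", so each level occurs once per drive. The stated benefit is that the design "allows for crash risk from using alcohol, cannabis, and alcohol and cannabis in combination to be assessed for avoidance scenarios of a range of difficulties". The primary measures named for these events are reaction time and time-to-collision; collisions are not among them.
- **Section 2.7.6, Figure 5 legend.** "The primary outcomes for these events are collisions, reaction time to the event, and time-to-collision with the event".
- **Section 2.7.1.** Collisions also appear as a count over the whole drive, within the accident category.
- **Section 2.6.** "Drives will be performed at baseline and again 1.5, 3.5, 5.5, and 7.5 h after Time 0", which is one baseline and four post-dose drives per session.
- **Section 2.1.** "All study participants will complete seven separate outpatient sessions", so every participant contributes to all seven conditions.
- **Section 2.14.** "Power analyses for each primary outcome were conducted in R", by simulation from linear mixed models with Cohen's d, means and SDs as inputs. The result reported is that "32 participants (16 men/16 women) in Part 1 and Part 2 would provide sufficient power", put at 0.80 or more. Outcomes are analysed with linear mixed models, two-sided at 0.05 with Holm-Bonferroni correction. The planned comparisons "compare mean peak change-from-baseline scores for each outcome".

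**The concern.** The legend and the body text of section 2.7.6 cannot both be the list of primary outcomes, and the choice matters. Under the legend, collisions fall within the section 2.14 power statement and within the peak change-from-baseline comparisons.

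Those tools suit reaction time and time-to-collision. They suit a collision at one difficulty level poorly. That outcome is 0 or 1 at each drive, so its peak change can only be -1, 0 or 1, and a participant who crashes at one post-dose drive scores the same as one who crashes at all four. The peak also picks up chance crashes from any of the four drives in both conditions, which dilutes the contrast.

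Collisions bear directly on the public-safety question that section 3 ties to per se limits. A non-significant result at one difficulty level, read beside a general claim of at least 0.80 power, would look more informative than it is.

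**Working it through.** **1. The plan's own figure.** The 0.80 cannot be reproduced, because no effect size, SD, correlation or crash rate is printed. For a continuous paired outcome with n = 32, the noncentral t distribution gives 0.80 power at a standardised paired difference of about 0.52 (two-sided 0.05), or about 0.66 at 0.05/6 (first Holm step if six contrasts are assumed). So 32 is not implausible for reaction time or time-to-collision.

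**2. Exposures per condition.** One level at one drive time: 32 × 1 = 32. One level over the post-dose drives: 32 × 4 = 128. All levels: 128 × 3 = 384.

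**3. Peak change at one level.** With Y = 1 for a collision, the score is D = max(Y1, Y2, Y3, Y4) − Y0, and each contrast is the mean within-person difference in D between two conditions.

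**4. Power for a doubled risk.** Everything here is assumed:
- logit P(collision) = condition-and-time term + person effect, with person effect SD 1;
- risks (baseline / 0.05% alcohol / co-use) of 5/7.5/15%, 5/10/20%, 10/15/30% and 10/20/40%, read as the risk of a participant of average tendency and taken as equal at the three levels;
- a paired t-test at two-sided 0.05;
- three time courses, given as the share of the drug's logit shift present at drives 1 to 4.

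| Share of effect at drives 1–4 | Peak change, one level | Count, three levels × four drives |
|---|---|---|
| 1, 0.5, 0, 0 | 0.09–0.16 | 0.28–0.62 |
| 1, 1, 0.5, 0.25 | 0.17–0.28 | 0.64–0.97 |
| 1, 1, 1, 1 | 0.28–0.38 | 0.91–1.00 |

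Repeated runs move these values by a few hundredths; the range over all of them for peak change is about 0.08 to 0.38. Post-dose collisions per level per condition ran from about 11 to about 53. The pooled count also had more power than a peak score of the whole-drive collision count in every time course.

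**5. Sensitivity to how the rates are read.** If the same percentages are population averages and the effect is constant over four drives, per-level peak change has 0.30–0.57 power (0.11–0.30 at 0.05/6). A separate run on population averages, with a constant effect and the pre-dose risk equal to the comparator's, gave:

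| Assumed risks | Peak change, one level | Count, one level, four drives | Count, three levels, four drives |
|---|---|---|---|
| 5 vs 10% | 0.21 | 0.32 | 0.73 |
| 10 vs 20% | 0.36 | 0.63 | 0.98 |
| 20 vs 40% | 0.48 | 0.96 | 1.00 |
| 10 vs 30% | 0.79 | 0.99 | 1.00 |
| 5 vs 20% | 0.84 | 0.96 | 1.00 |

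Much of the loss comes from the peak score itself. At 20 vs 40%, the same level and the same drives give 0.48 as a peak and 0.96 as a count.

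**The case against.** The strongest reply is that the power statement may not reach collisions at all. The body text of section 2.7.6 makes only the two continuous measures primary, the examples of crash-avoidance components in the composite score (section 2.7.8) are the same two, and section 2.7.1 treats collisions as a whole-drive summary. On that reading there is no power claim to fault. This stands, which is why the point begins with the inconsistency.

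Second, no collision test by difficulty level is named. Difficulty is not a model factor in section 2.14, and the crash-risk sentence describes what the scenarios permit. This also stands. The per-level score follows only from reading the legend, the crash-risk sentence and the comparison of each outcome together.

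Third, a reader might infer that each condition yields only a handful of collisions per level and that 0.80 power cannot hold. The documents do not support this. They print no crash rate; there are 128 post-dose exposures per level per condition, not 32; and three- to four-fold risks reach 0.79 to 0.84 even with the peak score.

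Fourth, the lowest power values assume an effect that has gone by the third post-dose drive. The introduction says that effects of edibles peak later and last longer than those of smoked cannabis, so that pattern should not be taken as given for Part 1, and an analysis confined to early drives could discard real effects. Nor does the article say that a null result at one level would be reported as no added crash risk.

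**Conclusion.** The point holds in a limited form. Section 2.7.6 contradicts itself on whether collisions are primary. If they are, section 2.14 gives them a linear model and a peak score that suit them badly, under a power statement whose basis for collisions is not shown.

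For a doubled risk at one difficulty level, peak change falls short of 0.80 in every scenario tried: about 0.08 to 0.38, and 0.57 at most if the rates are population averages and the effect lasts through all four drives. Pooling levels and drives was always better, although at 0.28 to 0.62 it too misses 0.80 when the effect fades quickly.

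These sizes rest on assumed crash rates, a person-effect SD of 1, equal risk across levels, assumed time courses and nominal alpha. They show that the power claim is unsupported for modest differences, not that it is false. The matter should be corrected, but it does not touch the continuous outcomes.

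**What to change.** 1. **Section 2.7.6:** make the legend and the body text agree on whether collisions are primary.
2. **Section 2.14, model:** analyse collisions with one repeated-measures logistic model (mixed or GEE) of all avoidance events. Include difficulty and drive time as factors and a condition contrast common to the three levels. Use all post-dose drives, or a window pre-specified separately for the oral and vaporized parts, in place of a peak score.
3. **Difficulty-specific results:** report condition-by-difficulty effects as exploratory estimates with confidence intervals, and word the crash-risk sentence in section 2.7.6 to match.
4. **Section 2.14, power:** limit the 0.80 statement so that it does not cover collisions by difficulty level. If collisions remain primary, give the pooled analysis its own power basis with stated crash rates.

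The cost is revised wording and one added model on data that will be collected anyway. Pooling assumes a similar relative effect across levels, which the interaction estimate can check, and difficulty-specific crash risk is no longer presented as a powered result.

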**FIGURE 5 F5:**
[figure not shown]
Crash avoidance events that occur throughout the drive for **(A,B)** human avoidance scenarios, and **(C,D)** vehicle avoidance scenarios. The primary outcomes for these events are collisions, reaction time to the event, and time-to-collision with the event.

Avoidance events are programmed to trigger based on the driver’s headway time from the object (e.g., pedestrian); easy, medium, and hard avoidances are set to headway times of 3.0, 2.5, and 2.0 s, respectively. Setting all avoidances based on headway time ensures a standard duration to react to a given avoidance (regardless of their approaching speed) and allows for direct comparisons across different types of avoidances. All avoidances were designed in ways that force participants to make a response and reduce the likelihood that they can ignore the avoidance. For example, for several avoidances, participants are constrained to a single lane at the time of appearance. The primary outcome measures for the crash avoidances are reaction time and time-to-collision (TTC) with the object. Reaction time to each avoidance is based on the participant’s initial response to the object after it appears, which could be a braking or steering response. TTC is calculated based on the participant’s distance from the object at the time of their initial response and their current speed at the time of their response (i.e., distance/speed = TTC).

#### 2.7.7 Stop light interaction tasks

Over the course of each drive, participants encounter eight stoplights, some of which are programmed to create two scenarios of interest: an amber light dilemma or a stoplight reaction test. The specific lights where these scenarios occur differ across the 10 drives. An amber light dilemma is a scenario in which a traffic light turns yellow as a driver approaches it and they must decide whether to stop or continue driving. This scenario has been conceptualized as a model of risk-taking; individuals who choose to continue driving in response to a yellow light risk running a red light, which may result in a traffic violation or crash in the intersection while those who choose to stop at the light may be considered more risk-averse (Palat and Delhomme, 2016; Pathivada and Perumal, 2019). During each drive, participants encounter two “true” amber dilemmas (one in a rural area and one in an urban area), meaning there is not necessarily a correct response; they can safely proceed through the light without receiving a penalty (e.g., a ticket) or can safely come to stop. All yellow lights are programmed to last 3.5 s, which is consistent with Maryland state traffic laws. For amber dilemmas, the stoplights are programmed to turn yellow when a participant’s vehicle is 3.5 s (in terms of headway time) from the light, thus maximizing the indecision zone (Figures 6A,B).

**FIGURE 6 F6:**
[figure not shown]
Stop light interactions for **(A,B)** amber dilemmas and **(C,D)** stop light reaction test that occur throughout the drive in rural and urban environments. During amber dilemmas, participants will approach a green light **(A)** that will change to yellow **(B)** 3.5 s from the intersection. During the stop light reaction test, participants will approach a green light that will change to yellow **(C)** 5.5 s from the intersection and then to red **(D)** 3.5 s after the yellow transition. The primary outcomes for these events are response to the traffic signal (i.e., stop or go through the light), reaction time to the signal light, and if participants stop, their response time to a green signal light.

The second stoplight scenario, the stoplight reaction test, is similar to the amber dilemma in that a traffic light turns yellow as a driver approaches. However, in this scenario, the light turns yellow much earlier (at a headway time of 5.5 s) and the correct response is for the participant to stop (Figures 6C,D). If they proceed through the light, they receive a ticket. Each drive contains one stoplight reaction test. The primary outcome measures for amber light dilemmas and stoplight reaction tests are reaction time to respond to the yellow light change (either gas or brake response) and whether the participant proceeded through or stopped at the light. For the stoplight reaction test, an additional outcome measure is reaction time to begin driving again in response to a green light (assuming the participant did not run the yellow light).

